# Streamlining staging of lung and colorectal cancer with whole body MRI; study protocols for two multicentre, non-randomised, single-arm, prospective diagnostic accuracy studies (Streamline C and Streamline L)

**DOI:** 10.1186/s12885-017-3281-x

**Published:** 2017-05-02

**Keywords:** Colorectal cancer, Lung cancer, Staging, Computed tomography, Whole body magnetic resonance imaging, Positron emission tomography, Patient experience

## Abstract

**Background and aims:**

Rapid and accurate cancer staging following diagnosis underpins patient management, in particular the identification of distant metastatic disease. Current staging guidelines recommend sequential deployment of various imaging platforms such as computerised tomography (CT) and positron emission tomography (PET) which can be time and resource intensive and onerous for patients. Recent studies demonstrate that whole body magnetic resonance Imaging (WB-MRI) may stage cancer efficiently in a single visit, with potentially greater accuracy than current staging investigations. The Streamline trials aim to evaluate whether WB-MRI increases per patient detection of metastases in non-small cell lung and colorectal cancer compared to standard staging pathways.

**Methods:**

The Streamline trials are multicentre, non-randomised, single-arm, prospective diagnostic accuracy studies with a novel design to capture patient management decisions during staging pathways. The two trials recruit adult patients with proven or highly suspected new diagnosis of primary colorectal (Streamline C) or non-small cell lung cancer (Streamline L) referred for staging. Patients undergo WB-MRI in addition to standard staging investigations. Strict blinding protocols are enforced for those interpreting the imaging. A first major treatment decision is made by the multi-disciplinary team prior to WB-MRI revelation based on standard staging investigations only, then based on the WB-MRI and any additional tests precipitated by WB-MRI, and finally based on all available test results. The reference standard is derived by a multidisciplinary consensus panel who assess 12 months of follow-up data to adjudicate on the TNM stage at diagnosis. Health psychology assessment of patients’ experiences of the cancer staging pathway will be undertaken via interviews and questionnaires. A cost (effectiveness) analysis of WB-MRI compared to standard staging pathways will be performed.

**Discussion:**

We describe a novel approach to radiologist and clinician blinding to ascertain the ‘true’ diagnostic accuracy of differing imaging pathways and discuss our approach to assessing the impact of WB-MRI on clinical decision making in real-time. The Streamline trials will compare WB-MRI and standard imaging pathways in the same patients, thereby informing the most accurate and efficient approach to staging.

**Trial registration:**

Streamline C ISRCTN43958015 (registered 25/7/2012). Streamline L ISRCTN50436483 (registered 31/7/2012).

## Background

Lung and colorectal cancer are the second and third most common malignancies in the UK, each accounting for 16% of all new cancer diagnoses; approximately 87,000 patients diagnosed per year [1]. Treatment decisions for both pivot on rapid and accurate tumour staging following diagnosis. In particular, detection of metastatic disease (i.e. disease which has disseminated beyond the primary tumour into distant organ sites such as bone, liver and brain) is vital for appropriate management.

In colorectal cancer, 50% of patients undergoing primary surgery with curative intent, relapse subsequently with metastatic disease, often within 12 months [2], in part reflecting sub-optimal staging following diagnosis. In lung cancer, over 20% of patients undergoing curative thoracotomy for presumed early stage disease relapse rapidly due to metastatic disease undetected by conventional staging tests – so called “futile thoracotomy” [3].

Cancer staging depends on high technology imaging platforms such as computerised tomography (CT), positron emission tomography (PET) and magnetic resonance imaging (MRI), together with standard scintigraphy, plain X- rays and ultrasound. Staging pathways are complex because these various modalities have differing diagnostic accuracies across different tumour types and body organs. The UK National Institute for Health and Care Excellence (NICE) guidelines outline an integrated but step-by-step sequential deployment of various imaging modalities before tumour staging is deemed complete and the first treatment decision is made [4]. It is not unusual for a patient with colorectal cancer to undergo CT chest, abdomen and pelvis, together with pelvic MRI in the case of rectal cancer, with additional tests such as ultrasound, MRI and PET-CT used increasingly in cases of known or suspected metastatic disease. Similarly, it is not unusual for a patient newly diagnosed with lung cancer to undergo standard chest and abdominal CT, whole body PET-CT, brain CT, and invasive mediastinal nodal sampling before the first definitive treatment decision. This stepwise multi-modality approach is both time and resource intensive, and onerous for patients at a very difficult time. Furthermore, patients receive significant doses of ionising radiation during the staging process that increase an individual’s risk of subsequent malignancy [5].

Recent technological advances allow whole body MRI scanning within one hour; sensitivity for metastatic disease is reported to be high [6–10]. MRI does not use ionising radiation and may be a safer, more efficient and accurate alternative to the standard multi-modality approach. There is little secondary research evidence concerning the accuracy of whole body MRI (WB-MRI) for cancer staging [11]. Meta- analysis is challenging because the WB-MRI primary literature comprises small single-centre cohort studies across a wide variety of cancers. These limited data do however indicate potential as an efficient and more accurate alternative for cancer staging. For example, NICE have recently recommended WB-MRI as first line in the initial staging of myeloma, due to higher accuracy compared to CT and standard skeletal survey [12]. The vast majority of available studies are however single site, using one MRI platform, with interpretation limited to one or two experienced radiologists. Generalisability is limited because most studies investigate single modality comparisons (e.g. WB-MRI vs. PET-CT) rather than comparing “real life” complex multi-modality staging pathways. Moreover, studies usually focus on diagnostic accuracy rather than therapeutic impact (i.e. the effect of testing on clinical decision making). Other limitations include frequent retrospective study designs, introducing bias.

This paper outlines the protocols of two multicentre studies comparing WB-MRI to standard NICE-approved diagnostic pathways for staging, (1) colorectal cancer –Streamline C (ISRCTN no: 43,958,015) and, (2) non-small cell lung cancer -Streamline L (ISCRTN no: 50,436,483). The studies are pragmatic and incorporate a variety of MRI platforms and interpreting radiologists, and assess the impact of WB-MRI on clinical decision making in real-time. In addition, the trials incorporate a health psychology assessment of patients’ experiences of WB-MRI, investigating potential impact on the physical and psychological burden of the cancer staging pathway, and predictors of patient preference. A detailed analysis of the cost and the cost-effectiveness of WB-MRI versus standard NICE-approved staging pathways will also be conducted. These trials are funded by the UK National Institute of Health Research (NIHR) Health Technology Assessment (HTA) programme, sponsored by University College London, and coordinated by the Cancer Research UK and UCL Cancer Trials Centre.

### Study objectives

#### Primary objective

To evaluate whether initial staging with whole body magnetic resonance Imaging (WB-MRI) increases per patient sensitivity for metastasis in colorectal and lung cancer compared to standard NICE-approved diagnostic pathways.

#### Secondary objectives

To determine how WB-MRI influences time to, and nature of, the first major treatment decision compared to standard investigations, and to determine whether early WB-MRI could reduce or replace standard investigations based on its diagnostic accuracy.To assess the accuracy of WB-MRI and standard diagnostic pathways for local and distant cancer staging. WB-MRI will be evaluated both as an additional test to standard pathways, and as a replacement test based per organ and per metastasis analysis.To determine the lifetime incremental cost and cost-effectiveness of staging using WB-MRI compared to standard diagnostic pathways.To evaluate patients’ experiences of staging using WB-MRI and to determine the priorities they place on differing attributes offered by competing staging pathways, including impact of reducing time to first treatment.To determine the inter-observer variability of WB-MRI diagnosis of metastatic disease by different radiologists and their confidence in diagnosis.To evaluate the diagnostic accuracy of WB-MRI protocols limited to diffusion and T1 weighted imaging only, and to assess the incremental benefit on diagnostic accuracy of intravenous gadolinium contrast enhancement.

## Methods

### General

Streamline C and Streamline L are parallel multi-centre prospective cohort studies comparing the staging accuracy of WB-MRI with standard pathways for newly diagnosed colorectal (Streamline C) and non-small cell lung cancer (Streamline L) conducted at 25 English National Health Service (NHS) hospitals. Data investigating the therapeutic impact of WB-MRI on patient management compared to standard pathways will be collated. The trial design compares two different staging strategies in the same patients ensuring comparable data are collected for both pathways while simultaneously increasing trial power to meet endpoints by using paired data.

Both qualitative and quantitative assessments will be employed to determine the psychological burden and acceptability of WB-MRI versus standard pathways, and to identify those attributes that influence patient preference most strongly. Health-related quality of life data is being collected, which will be used to inform cost-effectiveness modelling.

### Inclusions/exclusion criteria

Inclusion and exclusion criteria are outlined below. A series of imaging hubs will perform the WB-MRI according to the trial protocol (see below). Patients will be recruited from local hospitals (recruitment sites) and referred to the closest imaging hub for the WB-MRI. Some hospitals will act as both recruitment sites and imaging hubs.

In the colorectal cancer trial (Streamline C), eligible patients are aged 18 or older, able to give written informed consent, with histologically proven or strongly suspected colorectal cancer referred for staging (the latter defined as the presence of a mass highly suspicious for colorectal cancer on endoscopy, barium enema, CT colonography or other imaging which triggers staging investigations).

Patients with polyp cancer will be excluded because metastatic disease in these patients is exceedingly rare.

In the lung cancer trial (Streamline L), eligible patients are aged 18 or older, able to give written informed consent, with histologically proven or clinically diagnosed primary non-small cell lung cancer (NSCLC) with potentially radically treatable disease. Clinically diagnosed NSCLC cancer is defined as radiological diagnosis of lung cancer on chest CT with sufficient confidence to trigger staging investigations. Potentially radically treatable disease is defined as stage IIIb or less on diagnostic CT (i.e. T1–4, N0–2, M0). Patients should have a performance status 0 to 2 inclusive (and fit to undergo radical treatment if indicated). Patients with unequivocal metastatic or N3 disease on diagnostic CT chest and abdomen (including M1a disease; malignant pleural effusion) will be excluded as will those in whom further staging work up is not indicated due to poor performance status or patient choice. Those with histology other than non-small cell lung cancer will also be excluded given the differing biological behaviour of small cell lung cancer.

For both Streamline C and Streamline L, patients will be excluded if they have any psychiatric or other disorder likely to impact on informed consent, or evidence of severe or uncontrolled systemic disease, which make it undesirable for the patient to participate in the trial. Pregnant patients or others with contraindications to MRI (e.g. cardiac pacemaker, severe claustrophobia, inability to lie flat) are also excluded.

### Ethical arrangements and consent

The Streamline trials were approved by the London – Camden and King’s Cross Research Ethics Committee on 3rd October 2012 and are being conducted in accordance with the principles of ICH guidelines on good clinical practice in clinical trials and the Research Governance Framework for Health and Social Care (England). All patients give written informed consent prior to inclusion in the trials.

### Diagnostic interventions

#### Whole body MRI (WB-MRI)

The choice of MRI platform (i.e. manufacturer and Tesla (T) strength) will be decided by the local hub radiologist according to scanner availability and their usual clinical practice; either 1.5 T or 3 T platforms can be used. WB-MRI will be performed no later than 3 weeks after the final standard staging investigation. A minimum sequence dataset will be acquired including standard T1, T2 axial sequences supplemented by diffusion weighted (minimum 2 b-values, 50 and 900 s/mm^2^) and contrast enhanced T1 images through the liver, lungs and brain.

#### Standard imaging

Recruited patients will undergo all standard staging investigations employed at their hospital as per local protocols and requirements for usual care. The nature and date of these standard investigations (e.g. CT scan, PET-CT, organ specific MRI, biopsy etc.) will be recorded, along with the presence and location of any metastatic disease based on the radiological report, for later comparison.

### Blinding of WB-MRI reporters

WB-MRI will be reported by radiologists blinded to the results of standard imaging tests and other clinical information (other than the cancer diagnosis and site of the primary tumour). A novel approach employing a secure central imaging server (3Dnet™) provided by Biotronics3D (London, UK) has been employed to ensure the required level of blinding. Specifically, WB-MRI datasets will be anonymised by radiographer/technologists before upload from each hub to the secure central imaging server (3Dnet™). This solution enables rapid and simple upload of complex imaging datasets via a standard internet connection. Unanonymised WB-MRI images will only be released to the hospital picture and archiving system (PACS) after their revelation at the multi-disciplinary team (MDT) meeting (see below) so those reporting standard staging investigations are blinded to the WB-MRI images and findings.

### Interpretation and reporting

WB-MRI will be interpreted by designated trial radiologists who have prior experience in interpretation, defined as at least 20 validated WB-MRI cases in patients with lung or colon cancer. Radiologists with experience of less than 100 WB-MRI datasets will in addition undergo a period of “buddy” reporting with a more experienced radiologist (>100 WB-MRI datasets), and will only report alone once deemed competent by the more experienced radiologist. Interpretation may be performed using the 3Dnet™ viewing software or local workstations after download of the WB-MRI images, according to radiologist preference. A sequential viewing paradigm with ordered reading of selected sequences will used to examine the contribution of individual MRI sequences to radiologist diagnostic confidence and accuracy.

A free text clinical report will be produced based on all available sequences containing information relating to the local tumour (T), its nodal (N) stage, together with the presence, location, number and size of any metastatic deposits (M), as well as clinically important incidental findings, for example aortic aneurysm. The radiologist may recommend additional tests for equivocal findings as per their routine clinical practice.

### MDT review and influence of imaging on patient management

As per usual clinical practice, the MDT meeting will review all standard staging imaging initially blinded to the WB-MRI findings. MDT meetings will occur at least fortnightly, and usually weekly in a dedicated meeting room and as a minimum will include a radiologist, oncologist, histopathologist and respiratory physician and/or surgeon (Streamline L) or colorectal surgeon (Streamline C). It is anticipated that most MDT meetings will include more than one representative of these specialities. The MDT will have access to the full clinical record and histopathological data via the patient notes or electronic patient record, together with all standard imaging and reports via PACS. Based on this alone, the MDT will document the first major treatment decision (e.g. referral for surgical excision of the primary tumour, instigation of definitive treatment using chemotherapy, palliative/supportive care etc), as per usual care, along with the TMN stage.

The WB-MRI report and images will then be revealed to the MDT members by the MDT coordinator or designated representative via 3Dnet™ using an internet enabled PC (or via written paper copies in cases of IT failure). MDT members will evaluate the WB-MRI report and document any additional tests they deem the WB-MRI result generates (if any). If these additional tests have already been performed as part of the standard investigations, the MDT will then document the theoretical first major treatment decision based on the WB-MRI and results of the tests it would have generated. Finally, the MDT will then document their definitive first major treatment decision based on all available information (including the WB-MRI).

If the additional tests generated by the WB-MRI result have not already been performed as part of standard investigations and are deemed necessary by the MDT, these will be performed and the patients re discussed at the next scheduled MDT meeting when the process described above will be followed.

Occasionally a patient may commence definitive treatment before the date of a scheduled MDT such that the WB-MRI (and/or generated additional tests) will not yet have been revealed to the MDT. In this scenario, an ad hoc MDT will be convened consisting of all specialities relevant to the patient’s clinical care, and the MDT process described above will be followed.

### Early release of WB-MRI findings

The WB-MRI images and reports may be released early by reporting radiologists (ie before controlled revelation at the MDT meeting) if a diagnosis is made that potentially requires urgent intervention (specifically impending spinal cord compression, deep vein thrombosis or pulmonary embolism, or brain metastasis with significant mass effect requiring immediate treatment), or on request of the patient’s lead clinician for the patient’s clinical care in an emergency clinical situation. If early release precludes unbiased MDT assessment of the standard staging investigations, then the patient will be replaced.

### Time for staging

The total time taken to fully stage the patient using standard staging pathways will be calculated from the request date of the first staging investigation to the date of the MDT meeting’s first major treatment decision based on the standard imaging pathway. For Streamline L, the start of the staging process will be defined as the request date of the first staging investigation following a proven or highly suspected diagnosis of lung cancer (for example the date of requested PET/CT after diagnostic chest CT). For Streamline C, the start of the staging process will be defined as the request date of the first staging investigation following a proven or highly suspected diagnosis of colorectal cancer (for example the date of request for CT chest, abdomen and pelvis after colonoscopic diagnosis of likely malignant tumour). Because revelation of WB-MRI is deferred until after standard staging is complete, precise measurement of time to full staging using WB-MRI will not be possible. The theoretical time to complete staging using WB-MRI will be thus modelled taking into consideration the time from recruitment date to the date of the WB-MRI, plus the number and type of additional staging investigations generated by WB-MRI.

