#### Secondary outcome measures

The time and test number taken to reach, and the nature of, the first major treatment decision based on WB-MRI compared to standard staging pathwaysDiagnostic accuracy of WB-MRI and conventional staging pathways for local tumour staging and detection of metastasis. WB-MRI will be evaluated both as an additional test to standard pathways per patient, and as a replacement test based on per organ and per metastasis analysis.The lifetime incremental cost and cost-effectiveness of staging using WB-MRI compared to standard diagnostic pathwaysComparative patient experiences of staging using WB-MRI and standard investigations, and the average relative importance weighting of attributes ascribed to standard versus WB-MRI staging pathways.Inter-observer variability in WB-MRI accuracy and effect of radiologist diagnostic confidence on staging accuracy.Diagnostic accuracy of WB-MRI limited to T1 and diffusion weighted sequences compared to full WB-MRI protocols.

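### Standard staging time runs to an MDT decision, but the modelled WB-MRI time names no reporting or MDT interval, so the two are not like for like

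*Protocol article*

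**What the plan says.** Time for staging in the Protocol article describes both times in one paragraph. Standard time is "calculated from the request date of the first staging investigation to the date of the MDT"; the meeting meant is the one that decides on treatment from standard tests alone. The start event is then spelled out for each trial. For WB-MRI the article states that "precise measurement of time to full staging using WB-MRI will not be possible", because the result is withheld until standard staging is complete. A theoretical time will therefore be modelled "taking into consideration the time from recruitment date to the date of the WB-MRI, plus the number and type of additional staging investigations" that WB-MRI generates.

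The first item under Secondary outcome measures is "The time and test number taken to reach, and the nature of, the first major treatment decision", compared between WB-MRI and standard pathways. Secondary objectives frames the aim in the same way.

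On meeting frequency, MDT review and influence of imaging on patient management says that "MDT meetings will occur at least fortnightly, and usually weekly". Where WB-MRI prompts tests that are judged necessary and have not been done, "these will be performed and the patients re discussed at the next scheduled MDT meeting".

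**The concern.** The outcome is a time to a decision, and both pathways are meant to be compared on it. The standard time ends at a decision. The inputs named for the WB-MRI time end at the scan and the tests that it generates. A patient whose scan is complete has not been staged in the sense of the outcome until the scan is reported and a meeting has acted on it. If the model uses only the named inputs, part of any difference between pathways comes from where each clock stops.

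What is at stake is the interpretation of the first-listed secondary outcome. There is also a partial link to the discrete choice experiment: Health psychology assessment lists time to diagnosis among the attributes that differ between pathways, and sets attribute levels from accumulating trial data together with literature review.

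**Working it through.** The article gives no figure for staging time, so there is none to reproduce. The check sets the two definitions side by side and then sizes the missing step.

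**Side by side (Time for staging)**

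| | Standard | WB-MRI |
|---|---|---|
| Start | request of first staging test | recruitment |
| Tests | included, since the clock runs through them | scan date plus number and type of generated tests |
| Reporting | included, since the clock runs to the decision | not named |
| Wait for MDT | included | not named |
| Stop | MDT decision | no decision date named |

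**Size of the MDT wait**

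- Input: meeting interval T of 7 days (usual) or 14 days (longest allowed), from the MDT review section.
- Assumption: a patient becomes ready at a uniformly random point between two meetings. Mean wait = T/2; maximum = T.
- Weekly: 7/2 = 3.5 days, maximum 7.
- Fortnightly: 14/2 = 7 days, maximum 14.

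**A further MDT cycle, as a scenario only**

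- Let p be the share of patients whose WB-MRI generates necessary tests not already done. The article does not give p.
- If each such patient waits one more full interval, the mean addition is T/2 + pT.
- Weekly: 3.5 days at p = 0, and 3.5 + 7 = 10.5 days at p = 1. Fortnightly: 7 days at p = 0, and 7 + 14 = 21 days at p = 1.
- These upper ends are bounds, not estimates.

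**Forces in the other direction**

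The section on whole body MRI allows the scan up to three weeks after the last standard test. The recruitment-to-scan interval can therefore contain delay that comes from trial scheduling and lengthens the WB-MRI time. Its typical size is not given. The report interval, which would also be added to WB-MRI time, is not given either.

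**The case against.** The strongest reply is that the article lists inputs to a model and does not define a clock. The wording is not exhaustive, the limitation is disclosed, and a fuller analysis plan could add reporting and MDT intervals. That stands in part: the text does not exclude those steps. But deferred revelation explains why WB-MRI time has to be modelled, not why a decision step is named for one pathway and not for the other when the outcome is a time to decision.

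Three stronger readings are tempting, and the article does not support them.

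- *The different start dates are themselves a clear bias.* A trial WB-MRI would not ordinarily be requested before consent, so recruitment is a fair proxy for the request of that pathway's own first test. Starting WB-MRI at the first standard request would charge it with the delay to consent. The gap is not given. If it were assumed to be 0 to 14 days and added to the MDT wait, the total would be 3.5 to 17.5 days (weekly) or 7 to 21 days (fortnightly), but that sum should not be reported as bias.
- *Every patient with generated tests loses a whole extra cycle.* Re-discussion arises partly because the trial reveals WB-MRI only at the meeting, and it applies only to necessary tests not already done. Interpretation and reporting lets the radiologist recommend further tests, so in routine use some could be done before the first meeting.
- *The distortion feeds the economic model.* Cost effectiveness and Analysis describe resource use, quality of life, disease path and staging accuracy. Neither names staging time as an input.

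**Conclusion.** The concern holds for the stop point. As described, the standard time contains the wait for an MDT decision and the WB-MRI time does not, although the outcome is time to that decision for both. The omitted wait averages 3.5 days with weekly or 7 days with fortnightly meetings, on the assumption of uniform readiness; an unnamed report interval comes on top.

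Taken alone, this omission makes WB-MRI look faster. A reader might infer that the whole comparison therefore favours WB-MRI. That does not follow, because trial scheduling of the scan may lengthen the WB-MRI time by an amount the article does not give. The supported conclusion is that the comparison is not like for like and that its net direction is uncertain. It concerns a secondary outcome; the primary comparison of sensitivity is untouched.

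**What to change.** 1. **Stop point.** End both pathways at an MDT decision. For WB-MRI, add to the scan and generated tests a modelled report interval and the wait to the next scheduled meeting. As a companion comparison, stop both pathways at completion of the last staging test, which removes the MDT wait from both.
2. **Start point.** Start each pathway at the request of its own first staging test, and state that recruitment date stands in for the WB-MRI request.
3. **Sensitivity analysis.** Vary the report interval, the MDT wait and the scan wait. Show results with and without a further MDT cycle for patients whose WB-MRI generates necessary tests not already done. Where a full further cycle is added, do not also add the time for tests completed within it, or that time is counted twice.

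The cost is some modelling work and a somewhat longer WB-MRI time. Recruitment and conduct do not change, and Trial status says that the analysis is still to come. The article records dates of standard tests (Standard imaging) but does not say that report dates or routine MRI waits are held. Their availability should be checked, and any interval not on record should be entered as a stated assumption with a range.
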